## Abstract

**Background:**

The societal and personal burden of depressive illness is considerable. Despite the developments in treatment strategies, the effectiveness of both medication and psychotherapy is not ideal. Physical activity, including exercise, is a relatively cheap and non-harmful lifestyle intervention which lacks the side-effects of medication and does not require the introspective ability necessary for most psychotherapies. Several cohort studies and randomised controlled trials (RCTs) have been performed to establish the effect of physical activity on prevention and remission of depressive illness. However, recent meta-analysis's of all RCTs in this area showed conflicting results. The objective of the present article is to describe the design of a RCT examining the effect of exercise on depressive patients.

**Methods/Design:**

The EFFect Of Running Therapy on Depression in adults (EFFORT-D) is a RCT, studying the effectiveness of exercise therapy (running therapy (RT) or Nordic walking (NW)) on depression in adults, in addition to usual care. The study population consists of patients with depressive disorder, Hamilton Rating Scale for Depression (HRSD) ≥ 14, recruited from specialised mental health care. The experimental group receives the exercise intervention besides treatment as usual, the control group receives treatment as usual. The intervention program is a group-based, 1 h session, two times a week for 6 months and of increasing intensity. The control group only performs low intensive non-aerobic exercises. Measurements are performed at inclusion and at 3,6 and 12 months.

Primary outcome measure is reduction in depressive symptoms measured by the HRSD. Cardio-respiratory fitness is measured using a sub maximal cycling test, biometric information is gathered and blood samples are collected for metabolic parameters. Also, co-morbidity with pain, anxiety and personality traits is studied, as well as quality of life and cost-effectiveness.

**Discussion:**

Exercise in depression can be used as a standalone or as an add-on intervention. In specialised mental health care, chronic forms of depression, co-morbid anxiety or physical complaints and treatment resistance are common. An add-on strategy therefore seems the best choice. This is the first high quality large trial into the effectiveness of exercise as an add-on treatment for depression in adult patients in specialised mental health care.

**Trial registration:**

Netherlands Trial Register (NTR): NTR1894

## Background

Depression is a common disorder. The lifetime prevalence of depressive disorders in Dutch adults is 19% [1]. Recurrence of symptoms occurs in an unfavourable and fluctuating course in 44% and a severe chronic course in 32% of the patients. Depressive disorders obviously have negative effects on wellbeing and daily personal and professional functioning.

### Antidepressants and psychotherapy

Treatment frequently includes prescription of antidepressants. However, the effectiveness of such treatment may be limited because of poor compliance and limited effectiveness. A recent analysis of data of the US Food and Drugs Administration, showed relatively small drug-placebo differences in antidepressant efficacy [2]. Other disadvantages of antidepressants are unpleasant side effects and increased risk of hypertension in depressed patients combined with Diabetes Mellitus type II (DM II) [3,4].

A systematic review of randomised controlled trials into effectiveness and cost-effectiveness of brief psychological treatment for depression showed that some forms, especially cognitive-behavioural based approaches, were beneficial in the treatment of outpatients [5]. A meta-analysis, regarding a mostly adult population, found a favourable outcome for a combination of psychotherapy and pharmacotherapy compared to psychological treatment alone for depression in the short-term [6]. A recent meta-analysis examined whether the quality of the studies investigating psychotherapy for adult depression was associated with the effect-size found in these studies [7]. It showed that the effects of psychotherapy for adult depression have been overestimated in meta-analytical studies. The authors stated that the effects of psychotherapy are much smaller than is assumed.

The traditional treatment strategies, medication and psychotherapy, are still not ideal and a new intervention, exercise, focusing on a different psychopathological mechanism of depression is needed.

### Exercise

Exercise is a potential alternative low-cost therapy, but more studies are needed to define the place of exercise in a stepped care program for depression [8]. Exercise is relatively safe and has less negative side effects than antidepressants. Obviously, exercise has also many beneficial effects on physical health [9,10], and is expected to have additional advantages in depressed patients who suffer from a combination of mental and physical problems, such as pain complaints or increased risk of cardiac morbidity. Exercise is suitable for most individuals, participating in an exercise program promotes social integration and successful adaptation can increase self-esteem. Finally, exercise may reduce the negative side effects of antidepressants, such as fatigue, thus increasing compliance in medication use.

### Scientific evidence for the efficacy of exercise

Recent reviews and meta-analyses suggest that exercise leads to improvements in depressive symptoms [11,12]. Following the cumulative evidence from prospective cohort studies and RCTs, exercise has proven *protective *benefits for several aspects of mental health in general and for symptoms of depression in particular. However, study results on the *curative *effect on a present depression are conflicting. A recent Cochrane meta-analysis [13], updating an earlier systematic review in 2001 by Lawlor and Hopker [14], concluded that the statistically weak findings didn't support the efficacy of exercise in the treatment of depression. Methodological weaknesses of the trials were identified, including the lack of treatment concealment, intention to treat analysis and a clinical interview to confirm the diagnosis of depression.

Rethorst et al. [15] argue that the earlier mentioned meta-analysis of Lawlor and Hopker suffered from incomplete research data and a lack of moderating variable analysis. The meta-analysis by Rethorst et al., with 58 RCTs included, calculated an overall effect size of -0.80 for the effects of exercise on depression. The recommendation of both Lawlor et al. and Rethorst et al. is that further, conclusive research is still needed into the use of exercise for depression. Exercise as an adjunct to recognised treatments, such as psychotherapy and/or medication, should also be studied. Furthermore, follow-up research is needed that examines the sustainability of the effects after exercise therapy has ended.

Very recently, Krogh et al. [16] performed a systematic review and meta-analysis in which only 13 trials were selected because of the stringent selection criteria used (i.e. recording clinical depression according to any diagnostic system, adequate allocation concealment, blinded outcome and intention to treat analysis). Besides an inverse association between duration of intervention and the magnitude of the association of exercise with depression, the effect size was 0.40 for the pooled effect sizes of 13 studies and 0.19 for the selected three high quality design studies. The authors concluded that large high quality design studies are required. The recommendations from the three meta-analysis cited above are integrated in the design of the EFFORT-D study.

Besides reduction of depressive symptoms, exercise can be useful for other treatment indications, such as cardiovascular condition, metabolic syndrome, pain modulation and the immune system. Depression is associated with *cardiovascular disease*. It is an established risk factor for mortality after acute myocardial infarction. A recent meta-analysis of cohort studies also shows the aetiological and prognostic effects of depression on coronary heart disease (CHD) [17]: the pooled relative risk of depression on future coronary heart disease was 1.80. Another meta-analysis shows an overall relative risk of dying in depressed subjects of 1.80 compared to non-depressed subjects, with no major differences between men and women [18]. The increased relative risk on mortality was also found in subclinical forms of depression.

These findings suggest that exercise may also be prescribed to improve the cardiovascular condition and prevent future heart disease. Depressed patients should also be more closely monitored regarding cardiovascular parameters.

The body of evidence showing an association between depression and *obesity and metabolic deregulation *is growing. Recent meta-analysis of cross-sectional studies in the general population found a significant positive association between depression and obesity, affecting women more than men. A reciprocal risk relation between obesity and depression [19,20], and an U-shaped, non-linear trend in the association between BMI and depression was found [21]. The Dutch NESDA study [22] shows an association between severity of depression and unfavourable cholesterol high-hdl/low-ldl concentration [23]. This tendency for a higher risk of depression on metabolic syndrome, in which various cardiovascular risk factors appear, emphasizes the need of careful screening on this parameters [24], and exercise could positively influence these parameters.

A recent meta-analysis of studies into cytokines in depressed patients [25] showed that depression and an *activation of the immune-system *do co-exist. Both tumornecrosisfactor-α (TNF-α) and interleukine-6-concentration (IL-6) were significantly raised and C-reactive protein (CRP) was linearly associated with several conventional risk factors and inflammatory markers [26]. The relevance of CRP however still remains controversial [27]. Therefore, measurement of CRP blood levels in an intervention exercise study could contribute to a better understanding of the clinical importance in relation to heart condition.

The reciprocal relation between *pain and depression *has been reported in several studies where Major Depressive Disorder (MDD) was associated with chronic pain (> 6 months) and nearly 50% of patients had at least one chronic painful physical condition [28,29]. The duration of depressive symptoms was found to be prolonged in the presence of chronic pain. The therapeutic prognosis of co-morbid pain and depression is poor and the pain-depression association was found to be stronger in men than in women and in older adults compared to younger. Productivity was decreased when depression and pain existed in a co-morbid pattern [30].

### Quality of life and cost-effectiveness

Systematic evaluation of cost-effectiveness and quality of life, including life-events in the treatment of depression, may contribute to the development of more evidence based care models [31], for instance by disease management.

A population sample study showed that, in patients with a remitted MDD, the quality of life was lower than in the general population. A higher depressive severity was associated with a lower quality of life. Ten Doesschate et al. argue that, even in depression in remission, attention is needed for the quality of life, and above that, residual symptoms must be treated aggressively to achieve a higher quality of life [32].

### Summarized aims and hypothesis of EFFORT-D

The main objective of the study is to assess the effectiveness of exercise therapy (running therapy (RT) or Nordic walking (NW)), in addition to usual care, on depression in adult patients. We hypothesize that adding exercise therapy to usual care will result in a larger reduction in depressive symptoms (as measured with the Hamilton Rating Scale of Depression, (HRSD)) during a 6 month treatment program as well as at 6 months follow-up, compared to usual care without exercise therapy.

Secondary aims are to assess the effectiveness of exercise therapy (RT or NW) on the following outcome measures: 1) Cardiovascular and metabolic risk parameters as fitness (VO2 max, grip strength), BMI, waist circumference, body composition, blood pressure, fasting blood glucose, cholesterol HDL/LDL ratio and CRP, 2) Co-morbid symptoms of anxiety and pain 3) Quality of life, and 4) Cost-effectiveness.

To assess whether there are subgroups of patients who show a larger or less effect of exercise therapy on depression, subgroup analysis will be conducted differentiated on demographic variables (age, sex) and level and type of depression based on the HRSD, personality traits and level of fitness.

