## Methods/Design

EFFORT-D is a randomized controlled trial, designed along the Consort-statement guidelines [33], in which outpatients as well as hospitalised depressed patients will be included and randomized in two groups: a control group or an intervention group (*see flow chart in *Figure 1). The control group outpatients receive usual care (i.e. anti-depressive medication and/or cognitive and/or interpersonal therapy). The control group inpatients have their usual treatment program (consisting of pharmacotherapy and/or sociotherapy, psychotherapy, psycho-education and indicated nonverbal therapies) and are allowed to exercise at low intensity as part of their daily program.

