### Sample size

Following earlier RCTs [34] it is expected that patients in the usual care group (controls) will respond with a mean reduction in HRSD of six points. Adding exercise to usual care is expected to result in a decline of at least eight points in HRSD score (thus two extra points). To detect this difference, with an α (two-tailed) of 5% and a power (1-β) of 80%, using two equal groups and a standard deviation of 5 points, 100 patients are needed in each group. Taking 30% drop-out into account, 140 patients have to be included in each group.

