### Exercise intervention

The exercise sessions will take place twice a week (40 sessions in total): once a week a supervised group session is offered and once a week the patient does an individual training, with clear instructions beforehand and an evaluation at the beginning of the next supervised session. Each supervised session, in which the trainers are working according to a standardized protocol, lasts one hour, of which 30 min are spent running (RT)/Nordic walking (NW). The remaining time is spent on warming-up and cooling-down. Each patient follows an individualised intervention protocol with a gradually increasing training intensity. The goal is to achieve a 30 min period of continuous running in the last sessions (two times a week 30 min continuous aerobic exercise at least 60% of the maximal heart rate). The NW program follows a comparable progressive schedule with increased time spent Nordic walking with high intensity.

Intensity in RT as in NW is monitored by the instructor during every supervised session by counting the heart rate and three times during the intervention period by electronic registration (Polar RS 400, Electro Oy, Finland). The control group receives usual care for depression in accordance with the revised Dutch guideline [51] and are advised to exercise regularly. Hospitalised and day-care patients in the control group are supposed not to participate in organised high intensity aerobic exercise during the intervention period. Only low-intensity activity psycho-motor therapy is allowed.

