## Discussion

The aim of this study is to investigate the effectiveness of aerobic exercise therapy (RT or NW) on depression in adult patients in addition to usual care. Also, the effect of physical exercise on frequently existing co-morbid diseases or risk factors for such disorders as metabolic syndrome is an objective of this study.

This is the first well conducted add-on randomised controlled high-quality trial into the effect of aerobic exercise on depression with a correct randomisation procedure, blinded outcome assessment, intention to treat analysis, study into cost-effectiveness, quality of life and long-term follow-up as was advised in earlier publications. EFFORT-D can therefore contribute to stronger evidence for this type of intervention, which can result in more specified recommendations for clinical practice. Another strength of this study is the fact that also severely clinically depressed patients, who are mostly excluded in other studies, will be included. A relatively greater effect of exercise in this subgroup of severely depressed patients is possible. A challenge of the study lies in the motivational techniques needed to exercise with depressed patients, which is proven to be difficult [52] and it will take a serious effort not to exceed the calculated 30% drop-out patients in the intervention group. Because this study is supported by a strong hypothesis and minimal negative side effects are expected, one-tailed statistical analysis is also possible if the large number of included participants can't be reached within the planned time. Furthermore, the diversity of outcome measures makes it possible to distinguish more explicitly those depressed patients that could benefit most from exercise.

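### Care and control-group exercise rules differ by treatment setting, but setting is in neither the subgroup list nor the stated HRSD analysis, so a severity-by-treatment difference could partly reflect the comparator

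*Protocol article*

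**What the plan says.** All statements are from the protocol article.

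- **One pooled comparison.** Methods/Design describes a trial "in which outpatients as well as hospitalised depressed patients will be included and randomized in two groups".
- **Usual care differs by setting.** The same section gives outpatient controls medication and/or psychological therapy. Inpatient controls follow a ward programme that can also include sociotherapy, psycho-education and nonverbal therapies, with low-intensity exercise permitted.
- **Exercise rule for controls.** The Exercise intervention section encourages regular exercise in the control group as a whole and then adds: "Hospitalised and day-care patients in the control group are supposed not to participate in organised high intensity aerobic exercise during the intervention period". For those patients only low-intensity psycho-motor therapy is permitted. The Abstract instead describes a single low-intensity, non-aerobic rule for all controls.
- **Subgroups.** The aims section lists age, sex and "level and type of depression based on the HRSD, personality traits and level of fitness".
- **Analysis.** Statistical analyses compares mean HRSD by analysis of variance. It names usual physical activity, smoking and alcohol as confounders and allows unspecified adjustment for baseline differences. It contains no term for setting.
- **Randomisation** is done separately by location. Nothing says that location coincides with inpatient or outpatient status.
- **Expectation.** The Discussion, noting that severely depressed patients are included, says: "A relatively greater effect of exercise in this subgroup of severely depressed patients is possible".

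**The concern.** A subgroup analysis by severity asks whether the same contrast, exercise plus usual care against usual care, works better in more severe patients. Here the contrast itself may change with setting, because the background care and (on the Exercise intervention section's reading) the permitted control activity change with setting. If severity and setting are associated, a severity-by-treatment difference mixes two things: modification of the exercise effect by severity, and a difference between comparators. The plan names severity as a subgroup factor but omits the variable on which the comparator depends.

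The adjustment for usual physical activity does not settle this. Entered as a main effect, it adjusts the level of the outcome and leaves the treatment-by-severity interaction as it was. If post-baseline activity values were used, the model would also condition on something the intervention is meant to change.

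At stake is the interpretation of a secondary finding that the Discussion anticipates. A lesser point is that the pooled HRSD comparison carries between-setting variance that a baseline factor could remove.

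**Working it through.** **1. The plan's own figure.** Sample size uses a control response given as "will respond with a mean reduction in HRSD of six points", an expected response with exercise of "a decline of at least eight points in HRSD score (thus two extra points"), SD 5 and equal groups, "with an α (two-tailed) of 5% and a power (1-β) of 80"%.

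n per group = 2 × [5 × (1.960 + 0.842) / 2]² = 98.1, rounded up to 99, against 100 stated. Dropout of 30%: 98.1 / 0.7 = 140.2, against 140 stated. Both agree closely, and the sample size is not in question here. The inputs carried forward are the 2-point effect, SD 5 (variance 25) and 200 completers.

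**2. How far setting could change the contrast (assumed).** Suppose exercise truly gives 2 points everywhere and a share u of outpatient controls takes up exercise with full effect. The outpatient contrast is 2 − 2u:

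- u = 25%: 1.5 points, so the inpatient-minus-outpatient difference in effect is d = 0.5.
- u = 50%: 1.0 point, so d = 1.0.

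d can also be negative. The richer inpatient programme could shrink the inpatient contrast.

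**3. Artefact in the severity comparison.** With setting omitted:

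artefact = (inpatient share among severe − inpatient share among milder) × d

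The shares are assumptions, since the article gives no HRSD distribution by setting. At 70% and 10%: 0.6 × 0.5 = 0.3 and 0.6 × 1.0 = 0.6 points.

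**4. Precision of the severity interaction.** With N = 200, equal arms and a 50/50 severity split:

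SE = √(4 × 25/100 + 4 × 25/100) = 1.41

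- Artefact relative to SE: 0.3/1.41 = 0.2 and 0.6/1.41 = 0.4.
- Power for a true 2-point interaction: 29% (20% if one fifth of patients are severe).
- Interaction detectable with 80% power: 1.41 × 2.80 = about 4.0 points.

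Adding treatment-by-setting multiplies the variance by 1/(1 − φ²), where φ is the correlation between severity group and setting. At 70/10 the overall inpatient share is 0.4, φ = 0.6 × 0.25 / √(0.25 × 0.4 × 0.6) = 0.61, the factor is 1.6 and SE = 1.41 × √1.6 = 1.79.

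| Assumed inpatient share, severe / milder | Artefact at d = 0.5 | at d = 1 | at d = 2 | SE with treatment-by-setting |
|---|---|---|---|---|
| 30% / 30% | 0 | 0 | 0 | 1.41 |
| 50% / 20% | 0.15 | 0.30 | 0.60 | 1.49 |
| 60% / 10% | 0.25 | 0.50 | 1.00 | 1.66 |
| 70% / 10% | 0.30 | 0.60 | 1.20 | 1.79 |
| 80% / 10% | 0.35 | 0.70 | 1.40 | 1.99 |
| 90% / 10% | 0.40 | 0.80 | 1.60 | 2.36 |

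The d = 2 column needs either complete uptake with full effect among outpatient controls or some other equally large difference between settings. Negative d reverses every sign.

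**5. Precision of the primary comparison.** Share of variance explained by setting = f(1 − f) × Δ² / 25, with inpatient fraction f and between-setting difference in HRSD change Δ, both assumed:

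- f = 0.2, Δ = 2: 0.16 × 4 / 25 = 2.6%
- f = 0.3, Δ = 3: 0.21 × 9 / 25 = 7.6%
- f = 0.4, Δ = 4: 0.24 × 16 / 25 = 15.4%

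**The case against.** The strongest reply has four parts.

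**This is a condensed article.** The full protocol and analysis plan are not shown and may contain setting as a covariate or subgroup. That is fair as far as it goes, and the sponsor may be able to answer by confirming it. But the article itself fixes a subgroup list and a list of confounders, and itself makes care depend on setting, so the mismatch lies within what it states.

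**The link between severity and hospitalisation is not in the documents.** This stands. The HRSD entry threshold is the same for everyone. The exclusions remove long-stay patients, treatment-resistant inpatients and patients at high suicide risk on a closed ward, which may thin out the most ill inpatients. With equal shares the artefact is zero.

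**A stricter inpatient comparator is only one reading.** This also stands. The Abstract gives all controls one rule. No organised exercise is listed in outpatient usual care, so the inpatient limit may simply align the two control groups. Inpatient care is otherwise richer and could push the contrast the other way.

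**The artefact is small relative to noise.** At 0.3 to 0.6 points it is 0.2 to 0.4 standard errors, and a test of a 0.6-point interaction would be significant only about 7% of the time. The realistic risk is therefore a misread point estimate in a weak subgroup analysis, more than a false significant result.

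**Conclusion.** The concern holds in a limited form. Usual care and, as the Exercise intervention section reads, the control exercise rule differ by setting, and the stated plan takes no account of setting. If severity is associated with hospitalisation, a severity-by-treatment difference could partly reflect the comparator, in either direction. Under the assumed 70/10 shares and a 0.5 to 1.0 point difference in effect between settings, the size is 0.3 to 0.6 points, or 15% to 30% of the planned 2-point effect. The share and uptake figures are assumptions.

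A reader might go further in three ways that the documents do not support:

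- *That the two explanations cannot be separated.* Both settings are randomised and setting is knowable for every patient, so a treatment-by-setting term can separate them, at a loss of precision.
- *That a severity effect could be produced entirely by outpatient controls exercising.* The assumed artefact is a fraction of a standard error, its direction is open, and the Discussion says only that a larger effect in severe patients may occur.
- *That the main result is biased.* Randomisation protects the primary intention-to-treat comparison. Including setting would only improve its precision, by about 3% to 15% of variance under assumed inpatient shares of 20% to 40% and differences of 2 to 4 points.

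**What to change.** 1. Record inpatient, day-care or outpatient status at randomisation.
2. Include it as a fixed factor in the HRSD model.
3. Add treatment-by-setting to the planned subgroup analyses in the aims section.
4. Report the severity-by-treatment estimate with and without treatment-by-setting in the model, with confidence intervals, and label both exploratory. Do not require the severity effect to hold within each setting. At 70/10 shares and 200 completers, milder inpatients would number about 10% of 100 = 10, roughly 5 per arm, too few for such a rule.
5. Reconcile what the Abstract, Methods/Design and Exercise intervention sections say about exercise in the control group. Reconcile also the mention of day-care controls with the Study population section, which places day-care within an excluded category.

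The cost is one baseline field and a few sentences, with no change in sample size. The real price is precision: with 200 completers and a 50/50 severity split, the standard error of the severity interaction rises from 1.41 to about 1.5 to 2.4 points, depending on how strongly setting and severity are associated. If an unpublished analysis plan already contains these terms, confirming that is enough for items 1 to 4.
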